### Participants

The population from which the samples are recruited consists of consecutively admitted users of inpatient mental health care in the Canton of Zurich. Included are patients who

 – have been compulsorily admitted to psychiatry at least once during the past 24 months,

 – receive inpatient treatment in one of the four psychiatric hospitals participating in the study during the recruitment period (24 months),

 – are aged 18–65 years,

 – are residing in the Canton of Zurich,

 – and are willing and able to consent.

Patients who cannot be contacted by telephone (no telephone or mobile phone available) or who lack sufficient language skills are not eligible for inclusion.

Participation is not bound to a specific mental disorder. To be included in the study, however, patients must not have been diagnosed (index episode) with an organic mental disorder (ICD-10 F0), mental retardation (F7), a behavioural syndrome associated with physical factors (F5) or a developmental or behavioural disorder with onset usually occurring in childhood and adolescence (F8-F9).

The study sample is recruited from a naturalistic user sample from four study centres, all of them psychiatric hospitals mandated to provide psychiatric care to adult patients in the Canton of Zurich. Collaborating study centres are: Integrated Psychiatry Winterthur - Zürcher Unterland, Psychiatric Hospital Sanatorium Kilchberg AG, Clinic of Affective Disorders and General Psychiatry, Clinic for General and Social Psychiatry, Psychiatric University Hospital Zurich. At each study centre one designated mental health care worker is in charge of the study participants from that institution.

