#### Data analysis and statistical power

All major endpoints of the study will be compared between the intervention and the control group. Primary outcome of the study is the time in hospital accumulated over all involuntary inpatient stays during the 24 month period. This outcome criterion will be analysed in terms of both “time in hospital” and savings of health care budgets (“health care costs”).

As further endpoints of the study (secondary outcome criteria) changes in the perspective of the patients are assessed. Hypothesised benefits of the intervention are a reduction of institutionalised care and coercion. Lower levels of subjectively experienced coercion are supposed to be associated with a respective increase in quality of life, treatment satisfaction and level of empowerment.

To address the major research questions, the quantitative outcome data will be analysed for the whole trial across the four centres, using General Linear Models. T-tests for independent samples are applied primarily to test the comparability of the intervention and the control group. Analyses of covariance are performed to compare the intervention and the control group with respect to the primary outcome (time in hospital accumulated over all involuntary inpatient stays) and secondary outcomes (reduction in levels of subjectively experienced coercion; increase in quality of life, treatment satisfaction and level of empowerment). Age, gender, centre and other variables which show significant between-group differences are included in the GLM models as covariates. To examine which characteristics on the patient level (treatment history, diagnosis, social network, treatment adherence in the two-year follow-up) modify the outcome, we examine the effects of these variables on the outcomes of interest within the intervention group, applying regression analyses. The level of significance is set at 0.05, two-tailed.

The planned overall sample size across all centres is 400 patients, of which 200 each will be assigned to the intervention group or to the control group. So each centre is expected to contribute 100 patients (50 intervention group and 50 control group).

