Power analyses revealed that these sample sizes will be large enough to identify significant differences in the primary outcome criterion (length of compulsory inpatient episodes) between the intervention and the control group. For power analysis, length-of-stay data from the Psychiatric University Hospital Zurich over the period 2007–2008 were used. Compulsorily admitted patients (with the same diagnostic spectrum and age range as the sample considered for inclusion) stayed a mean length of 33 days (SD 42 days; CV 1.25) during a 24-month period. A log-normal distribution for the length of stay was assumed. A two-sample t-test on the mean ratio was performed to calculate the sample size on the basis of these data. The probability of type I error was set at 5% and probability of type II error at 20%. An 8–day reduction of the mean length of compulsory inpatient time due to the study intervention (approximating a quarter of inpatient time) was considered a clinically relevant difference. For confirming a reduction of the mean length of compulsory inpatient time from 33 days to 25 days a sample size of 193 in each (intervention and control) group would need to be treated (total sample size of 386).

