### Preliminary reflections on the limitations and strength of the study

A limitation of the study may be that long-term engagement in an intensive programme such as the one proposed may be difficult for patients with serious mental disorders. A selection bias at inclusion may be expected as a result of the consent procedure and during the follow-up as a result of dropouts. An advantage of the study, however, is that patients who have previously experienced compulsory measures in psychiatry may now have a strong interest to participate in such a programme in order to avoid further compulsory admission.

To determine dropout effects, differences between patients included in the study and those not included, but eligible for inclusion (to be traced by means of the respective hospital statistics) will be analysed. Likewise, patients who finish the programme and those who drop out during follow-up will be compared with respect to psychopathological, social and health care characteristics. We thus hope to better understand which patients might qualify for such a programme and to what extent results can be generalised. If dropout analysis does not reveal any systematic bias, the results likely may be generalised for a population of mentally ill at risk for involuntary psychiatric care.

Long-term engagement (24-month preventive monitoring), on the other hand, might be a strength of this study. Advance directives alone do not necessarily impact the outcome of care, as the study by Papageorgiou et al. [12] suggests. There are several reasons attributable to peculiarities on the part of the mental health care system, as well as on the part of patient behaviours, as to why directives might be ignored. It is considered a meaningful and integral part of this trial, therefore, to follow patients after hospital discharge, all the more so as a considerable number of this patient group holds reservations towards visiting an outpatient mental health professional. In this situation, a preventive monitoring may have beneficial effects, bringing to mind betimes the patient’s individual action plan in case of a crisis and motivating them to continue treatment.

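### The 193 per group is sized on patients who all had a compulsory admission and on a distribution without zeros, so the 80% power is unsupported for post-discharge involuntary days, and only 3.5% is spare for lost outcome data

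*Protocol article*

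**What the plan says.** All places are in the protocol article.

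- **Outcome** (Data analysis and statistical power): "Primary outcome of the study is the time in hospital accumulated over all involuntary inpatient stays during the 24 month period".
- **Entry** (Participants): patients must "have been compulsorily admitted to psychiatry at least once during the past 24 months" and be inpatients in a study hospital. A new compulsory admission is not required.
- **Period** (Intervention, part c; Study design): the intervention lasts 24 months, and telephone monitoring covers 24 months from discharge from the index episode.
- **Planning data** (Data analysis and statistical power): "Compulsorily admitted patients (with the same diagnostic spectrum and age range as the sample considered for inclusion) stayed a mean length of 33 days", with SD 42 and CV 1.25 over 24 months, from one hospital in 2007–2008. The distribution is taken as log-normal and the test is a t-test on the mean ratio.
- **Target**: 33 to 25 days. These 8 days are described as roughly a quarter of inpatient time.
- **Size**: "a sample size of 193 in each (intervention and control) group would need to be treated (total sample size of 386"; 400 are to be enrolled, 200 per group. Type I error is 5% and type II error 20%; "The level of significance is set at 0.05, two-tailed".
- **Dropout** (Preliminary reflections on the limitations and strength of the study): "A selection bias at inclusion may be expected as a result of the consent procedure and during the follow-up as a result of dropouts". No rate is given.

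**The concern.** The planning sample was selected on having the event. Each person in it has at least one compulsory stay, and a log-normal variable cannot be zero. In the trial, the compulsory admission that qualifies a patient lies before follow-up, and the outcome counts what happens afterwards. The programme aims to prevent compulsory admission, so its intended success is a patient with zero days, which is the one value the sizing model excludes.

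The article nevertheless concludes that the sample is large enough. That statement justifies 400 patients and would be used to read a null result. If many participants have no involuntary days, a null result could not be told apart from low power. The small gap between 386 and 400 adds to this, because the article itself expects dropouts over two years.

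**Working it through.** **1. The plan's own figure.** Inputs: CV 1.25, means 33 and 25, two-sided 5%, 80% power.

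- Log-scale SD: σ = √ln(1 + 1.25²) = 0.970. Log mean ratio: δ = ln(33/25) = 0.278.
- Normal approximation: n = 2(σ/δ)²(1.960 + 0.842)² = 191.6, so 192 per group. The noncentral t gives 193, an exact match.
- With 200 complete patients per group, the power on this model is 81.5%.

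The arithmetic is right. The question is whether the inputs describe the outcome.

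**2. Planning data against outcome.**

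| | Planning data | Trial outcome |
|---|---|---|
| Who | compulsorily admitted patients | inpatients with a compulsory admission in the past 24 months |
| Window | calendar 2007–2008, one hospital | 24 months after index discharge |
| Smallest value | above zero | zero if not compulsorily re-admitted |

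**3. What zeros do to power.** The documents give no share of zeros, so 30% and 50% are assumptions. Control patients with any involuntary days follow the planning distribution (log-normal, mean 33, CV 1.25), also an assumption. There are 200 per group, no dropout, and 20,000 simulated trials per cell; the test is a two-sided 5% t-test. The effect either shortens stays (same zeros, lower mean when positive) or prevents admissions (more zeros, same mean when positive).

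Control means are 0.7 × 33 = 23.1 and 0.5 × 33 = 16.5 days. Eight days are then 8/23.1 = 35% and 8/16.5 = 48% of the control mean.

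| Zeros | Reduction held | Route | Power on days | Power on log(1+days) |
|---|---|---|---|---|
| 30% | ratio 25/33 | shorter stays | 40.4% | 21.1% |
| 30% | ratio 25/33 | fewer admissions | 37.2% | 88.7% |
| 50% | ratio 25/33 | shorter stays | 27.9% | 12.5% |
| 50% | ratio 25/33 | fewer admissions | 26.3% | 62.1% |
| 30% | 8 days | shorter stays | 74.8% | 43.2% |
| 30% | 8 days | fewer admissions | 66.5% | 99.5% |
| 50% | 8 days | shorter stays | 90.0% | 49.2% |
| 50% | 8 days | fewer admissions | 80.3% | 99.8% |

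Shorter simulation runs move these by one or two points. Not all of the fall on the days scale is due to zeros: with no zeros, the test on days already has only about 62%, against about 81% on the log scale used for sizing. The article plans analysis of covariance and names no transformation, so both scales are shown.

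**4. Reserve for lost outcomes.** (400 − 386)/400 = 3.5%. On the plan's own log-normal model, with assumed loss rates:

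| Loss | Per group | Power |
|---|---|---|
| 0% | 200 | 81.5% |
| 5% | 190 | 79.5% |
| 10% | 180 | 77% |
| 20% | 160 | 72% |
| 30% | 140 | 67% |

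**The case against.** **The documents do not state the mismatch outright.** They do not say that the qualifying stay is included in the 33 days, nor that remaining index days are excluded from the outcome. This stands as a caveat. The natural reading of the sections on the intervention, design, participants and analysis is nevertheless post-discharge days.

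**The control mean need not be below 33.** The planning data cover one hospital and a fixed calendar window, so stays elsewhere or running past the window may be missed. The trial follows each patient for 24 months across services and enrols current inpatients. These features could raise the mean. This stands, and the mean-when-positive used above is an assumption. It does not put zeros into the planning data.

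**Power depends on which target is kept.** The article names 8 days as the relevant difference. Holding 8 days restores about 80% or more on days at 50% zeros. This also stands, but the article justifies 8 days as about a quarter, and 48% is not a quarter.

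**Dropping out of the programme is not the same as losing hospital-day data**, and a retention assumption may sit in the full protocol. This is fair, so the reserve is described here as one for lost outcome data.

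**Two stronger inferences do not hold.** A reader might divide 42 by 33, get 1.27 and call the CV of 1.25 an error. Means of 32.5–33.5 and SDs of 41.5–42.5 give CVs of 1.24–1.31, so rounding explains it. A reader might also put the CV of a zero mixture into the log-normal formula to obtain a new sample size. That formula cannot represent zeros, so the result would describe no actual test.

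**Conclusion.** The concern holds in this form: 193 per group is correct arithmetic on inputs that do not describe the primary outcome. The 80% power is unsupported for involuntary days after discharge and probably too high for a reduction of about a quarter. At an assumed 30% or 50% zeros, power on days is about 37–40% or 26–28%. On log(1+days) it ranges from well below 80% to 89% at 30% zeros, and reaches at most about 62% at 50%.

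A reader might infer that the trial is shown to lack 80% power. The documents do not support that, because the zero share, the attrition rate and the route of the effect are not given, and some scenarios keep 80%: an effect wholly through fewer admissions, analysed on log(1+days) at 30% zeros, or a fixed 8-day reduction at 50% zeros.

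The reserve of 3.5% follows directly from the article's figures. On the plan's own model, about 5% loss of outcome data is enough to fall just below 80%.

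**What to change.** - Re-extract the planning figures from the same hospital's data as the trial defines the outcome: involuntary days in the 24 months after discharge, among patients with a compulsory admission in the prior 24 months, zeros included and the qualifying stay excluded. A 24-month look-back plus 24 months forward does not fit within 2007–2008, so the extract must span more years.
- By simulation from that distribution, restate the power of 400 patients and the detectable reduction for the planned analysis, with a stated attrition rate. Say whether the target is a relative reduction of about a quarter or an absolute 8 days.
- Replace the claim that 193 per group gives 80% power.
- Optionally, complete the primary outcome from hospital records for all randomised patients. The article already plans to use hospital statistics to trace eligible non-participants.

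The cost is one data extraction from a source already used and a rewritten power statement. No extra patients are needed, and allocation and endpoint stay as they are. The stated power will probably become less favourable.

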## Discussion

The current study aims to prevent compulsory admission to psychiatric hospital and to reduce patients’ perceived coercion by offering an intervention programme consisting of individualised psycho-education and a 24-month preventive monitoring after inpatient admission. The intervention hereby intends to increase patient satisfaction, quality of life and empowerment in patients with serious mental disorders and previous compulsory psychiatric admission(s). Detailed follow-up assessments of service use, psychopathology and patients’ perceptions are scheduled 12 and 24 months after discharge. The intervention programme will be compared with standard care procedures in order to prove its effectiveness (in terms of “time in hospital” in connection with involuntary inpatient episodes, perceived coercion, empowerment, treatment satisfaction, quality of life) and cost-effectiveness (in terms of cost-containment in inpatient mental health care). Moreover the study seeks to identify individual and social factors that influence primary and secondary outcomes.

### Preliminary reflections on the limitations and strength of the study

A limitation of the study may be that long-term engagement in an intensive programme such as the one proposed may be difficult for patients with serious mental disorders. A selection bias at inclusion may be expected as a result of the consent procedure and during the follow-up as a result of dropouts. An advantage of the study, however, is that patients who have previously experienced compulsory measures in psychiatry may now have a strong interest to participate in such a programme in order to avoid further compulsory admission.

To determine dropout effects, differences between patients included in the study and those not included, but eligible for inclusion (to be traced by means of the respective hospital statistics) will be analysed. Likewise, patients who finish the programme and those who drop out during follow-up will be compared with respect to psychopathological, social and health care characteristics. We thus hope to better understand which patients might qualify for such a programme and to what extent results can be generalised. If dropout analysis does not reveal any systematic bias, the results likely may be generalised for a population of mentally ill at risk for involuntary psychiatric care.

Long-term engagement (24-month preventive monitoring), on the other hand, might be a strength of this study. Advance directives alone do not necessarily impact the outcome of care, as the study by Papageorgiou et al. [12] suggests. There are several reasons attributable to peculiarities on the part of the mental health care system, as well as on the part of patient behaviours, as to why directives might be ignored. It is considered a meaningful and integral part of this trial, therefore, to follow patients after hospital discharge, all the more so as a considerable number of this patient group holds reservations towards visiting an outpatient mental health professional. In this situation, a preventive monitoring may have beneficial effects, bringing to mind betimes the patient’s individual action plan in case of a crisis and motivating them to continue treatment.

A further general limitation relates to the fact that with such a programme only those factors that contribute to compulsory admission which are subject to the patient’s self management can be modified. Compulsory admission to a psychiatric hospital of course does not depend only on a patient’s clinical status and characteristics of his/her psychosocial background. Rather, service system aspects that determine referral or crisis intervention procedures might have a share in the use of involuntary placement. With the current intervention programme only risk factors that can be governed by the patients themselves might be reduced, whereas further steps would have to be taken in order to effect a change in service system aspects. The effectiveness of preventive measures focusing on compulsory admission so far has only rarely been studied in larger samples. A strong point of this study lies in the opportunity to conduct a prospective analysis using a controlled randomised design. In Switzerland, the number of compulsory admissions has remained at an exceedingly high level for a long time. This is an unacceptable situation which necessitates the testing and the analysis of interventions targeting the factors that might be amenable to change in order to reduce the rate of involuntary placements. The present study focuses on the continuity of care after discharge from psychiatric hospital, in particular on measures which may increase treatment adherence or pharmacological drug compliance. These measures, aiming at the activation of the patients’ potential for secondary prevention of relapses by increasing the self-management skills of chronically mentally ill patients, appear to be a new and innovative strategy to prevent involuntary inpatient episodes.
